## Abstract

**Introduction:**

Cardiovascular diseases are a common chronic illness in adults, with implications for health and psychological well-being. These implications not only affect the patients themselves but also impact family members, especially the spouses of patients. One significant issue and consequence of this disease is its impact on marital relationships and sexual satisfaction, which can also influence other dimensions of quality of life. The aim of the current study is to determine the effect of couple counseling based on the CHARMS model on sexual quality of life and marital satisfaction of wives of men suffering from myocardial infarction.

**Method:**

This study is a clinical randomized controlled trial. Sampling will be done on a convenience basis. Participants will be randomly allocated into two groups: control (50 couples) and intervention (50 couples). Couples in 6 groups of 8 members each will attend counseling sessions based con the CHARMS model, with sessions held weekly and lasting for 60 min. Data collection tools will include Demographic information questionnaire, Women’s Sexual Quality of Life Questionnaire, Enrich Marital Satisfaction Questionnaire, Sexual Compatibility Questionnaire and Perceived Quality of Relationship Dimensions Questionnaire, which will be completed by women in both groups before and after the intervention. Data will be analyzed using appropriate statistical tests and SPSS software.

**Discussion:**

This trial will evaluate whether a counseling intervention based on the CHARMS model can enhance sexual quality of life and marital satisfaction of wives of men with myocardial infarction in Urmia city.

**Trial registration:**

IRCT code: IRCT20240218061046N1

## Introduction

Cardiovascular diseases are among the most prevalent chronic conditions and a leading cause of death and disability in adults globally [1]. The incidence of this disease doubles with each decade of life. Cardiovascular diseases, with an annual mortality rate exceeding 17 million people worldwide, rank first globally, particularly impacting low and middle income countries. It is projected that cardiovascular diseases will account for over 23 million deaths annually worldwide by 2030 [2]. Official data indicates a rising trend in mortality rates due to this issue in Iran as well [3]. Given the severe and chronic nature of cardiovascular diseases, they present a crisis in the affected individual’s life, significantly affecting not only their physical health but also their psychological well-being [4]. These diseases are recognized as key factors influencing individuals’ sexual lives in terms of quality, performance, and satisfaction. Sexual dysfunction and decreased sexual activity are prevalent among heart patients, impacting their overall sexual quality of life [5]. A primary sexual issue reported by heart patients is a decline or loss of sexual desire, often linked to concerns such as anxiety about sudden death during sexual activity, misinterpretation of normal signs of sexual arousal as cardiac symptoms like increased heart rate and breathing, and depression following a heart attack. Ultimately, this results in sexual dissatisfaction, poses risks to mental health, and consequently disrupts family unity [6].

The quality of marital relationships is a multidimensional concept that includes compatibility, sexual satisfaction, happiness, harmony, and commitment among couples. However, individuals with ischemic heart diseases may face challenges in their marital relationships due to fear and confusion about the impact of the illness. This can result in decreased satisfaction, reduced intimacy, and avoidance of social activities. Research indicates that the frequency of sexual relationships among patients with ischemic heart diseases can decrease by 40 to 70% [7].

Studies have indicated that ischemic heart diseases have a significant impact on the intimate relationships between couples. Many spouses of heart patients feel they are in a critical situation and want to reassure their partners of their love, but they are concerned about the consequences of sexual activity. This concern can result in the avoidance of sexual relationships, despite the importance of sexual activity to individuals’ quality of life [5, 7].

Patients with heart disease may be uncertain about the effects of sexual activity on the heart, and partners may generally avoid sexual intercourse due to fear of its consequences [8]. A decrease in the quality and frequency of sexual relationships has been observed in men following myocardial infarction (MI), along with a notable reduction in the frequency of sexual activity and sexual satisfaction [9]. Sexual dysfunction in men who have survived heart attacks can manifest as decreased libido, erectile dysfunction, and premature ejaculation [7]. Sexual education is crucial for patients and should commence in the acute phase of the disease, continuing throughout the recovery period. Studies have shown that men prioritize receiving information about the timing of sexual activity as part of their educational needs [10]. However, conversations about sexual matters among hospitalized cardiac patients are often stifled by shame, modesty, and cultural barriers, resulting in the neglect of sexual counseling, which is a vital aspect of nursing counseling [11].

Since all stages of sexual activity are accompanied by an increase in heart rate, which can lead to the manifestation of a heart attack experience and fear of a recurrent heart attack in patients, preventing such challenges and sexual concerns in patients requires creating awareness and counseling to explore and address sexual anxieties [12]. However, sexual rehabilitation after heart disease has been largely overlooked, and even discussing sexual issues during medical visits is perceived as difficult by both patients and physicians. Studies indicate that recommendations given to patients regarding resuming sexual activity after acute cardiac events or surgery are variable and insufficient, leading many patients to struggle with the fear of engaging in sexual intercourse [13] Therefore, it is essential to provide appropriate planning and sexual counseling tailored to each patient’s condition to enhance the sexual health of cardiac patients. The use of sexual counseling methods helps patients maintain their emotional relationship with their spouse despite all the physical and psychological changes related to their conditions and enables them to have a satisfying sexual life [14].

Models are guidelines that assist healthcare providers in implementing appropriate and effective supportive interventions and solutions for health concerns and issues such as sexual problems in patients [15]. One of the activities that should be included in cardiac rehabilitation programs is sexual counseling within the framework of cardiac rehabilitation programs. The goal of providing sexual counseling to cardiac patients is to assess existing sexual problems, provide information about concerns and safety in sexual activity after a cardiac event or process [16]. The American Heart Association and the European Society of Cardiology recommend that all patients with cardiovascular diseases should be evaluated for sexual concerns and offered free sexual counseling. Among the recommended counseling methods by these associations that can be helpful is the CHARMS-based counseling method (Cardiac Health and Relationship Management and Sexuality) [17].

A CHARMS-based intervention with 4 principles addresses the sexual and marital relationship empowerment of couples following a severe heart attack. These principles include: (1) Counseling and providing information on the impact of cardiovascular diseases on sexual desires. (2) Counseling and providing information on a healthy sexual life and communication skills strategies with the sexual partner. (3) Counseling on uncovering false beliefs and misconceptions regarding relationship risks and fears. (4) Providing tips and solutions for resuming sexual relations after a severe heart event, addressing sexual and interpersonal challenges. This intervention sets patients’ expectations of sexual relationships based on a final focus on “sexual intimacy” as the ultimate goal of therapy [18].

Considering the prevailing culture in Iranian families where marital relationships are perceived as personal and private, the quality of sexual relationships is not usually assessed in medical treatment programs or even in the follow-ups of cardiac patients. Studies conducted in Iran descriptively examine the sexual problems of cardiac patients, with few intervention studies focusing on the impact of treatment methods on their sexual quality of life.

### General objective

To determine the impact of couple counseling based on the CHARMS model on sexual quality of life and marital satisfaction of wives of men with myocardial infarction.

### Specific objectives

To determine and compare the average score of sexual quality of life of wives of men with myocardial infarction before and after the intervention in two groups.To determine and compare the average score of marital satisfaction of wives of men with myocardial infarction before and after the intervention in two groups.

### Practical objective

It is expected that through the current research and confirmation of the effects of couple counseling based on the CHARMS model on sexual quality of life and marital satisfaction of wives of men with myocardial infarction, this method and intervention will be utilized by women’s health and midwifery specialists, maternity experts, and nurses working in healthcare centers. This will enable an important step towards improving the sexual quality of life and marital satisfaction of these wives through the use of models and guidelines.

### Research hypothesis

Couple counseling based on the CHARMS model leads to an increase in the average score of sexual quality of life and marital satisfaction in wives of men with myocardial infarction.

## Methods

The present study is a clinical trial aimed at determining the impact of couple counseling based on the CHARMS model on sexual quality of life and marital satisfaction of wives of men with myocardial infarction in Urmia city.

### Inclusion and exclusion criteria

The inclusion criteria for couples in the study include: definite diagnosis of heart attack and a minimum of 6 months since its occurrence in men, first-time heart attack in men, living with the spouse during the study period, no history of mental or emotional trauma in the past 6 months, no history of chronic disease in women, having children, residing in Urmia city, having at least primary education, age between 35 and 55 years in spouse, and not participating in similar research projects in the past three months. The exclusion criteria include not attending counseling sessions more than once and withdrawing from continued cooperation and changing the city of residence during the study period.

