### Sampling and data collection

Samples will be selected using convenience sampling and divided into two groups: intervention (45 couples) and control (45 couples) based on even and odd numbers in sealed envelopes. The participants will be asked to choose an envelope, in such a way that even numbers inside the envelope correspond to the intervention group and odd numbers belong to the control group.

Researchers will visit the Seyyed Al-Shohada Hospital in Urmia after obtaining official approval from the Ethics Committee of Urmia University of Medical Sciences. After introducing the research, explaining the objectives and methods to the patients, eligible individuals will be selected. Upon their agreement to participate, informed written consent will be obtained from both men and their spouses. Subsequently, the couples’ phone numbers will be collected for scheduling counseling sessions. Researchers will emphasize the importance of couples attending counseling sessions together.

A couple participated in sessions within 6 groups, each consisting of 8 members, held weekly for 60 min. After collecting participants’ phone numbers, it was arranged for them to be prepared for 6 sessions of sexual counseling based on the CHARMS method. The intervention program was designed based on the CHARMS empowerment program and following similar studies [17].This intervention includes: (1) sexual education and counseling for spouses of patients with heart attacks, (2) educational and supportive intervention for heart attack patients by researchers and nurses in the cardiac rehabilitation program, (3) delivering informative booklets to patients, and (4) providing pamphlets on the topics of each session to increase awareness among heart attack patients and their spouses.

The content of each counseling and educational session was compiled by the research team from books, articles, websites, and reputable sources such as: European Society of Cardiology and American Heart Association [26–31] (Table 1).

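### Couples are excluded after allocation for missing more than one counselling session, a rule only the intervention arm can trigger, so randomisation no longer protects the comparison

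*Protocol article*

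**What the plan says.** Under Inclusion and exclusion criteria, the article gives three grounds for exclusion. The first two concern attendance and withdrawal: "The exclusion criteria include not attending counseling sessions more than once and withdrawing from continued cooperation". The third is "changing the city of residence during the study period". All three are events during the study; none can be known when a couple draws an allocation envelope.

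Under Sampling and data collection, couples are to be "prepared for 6 sessions of sexual counseling based on the CHARMS method", and the sessions are described as the content of the intervention: "The intervention program was designed based on the CHARMS empowerment program". Neither that section nor Table 1 describes sessions or an attendance duty for controls. Controls complete the questionnaires before the intervention period and again one month after it ends.

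Under Data analysis, the groups are compared by independent t-test or Mann-Whitney test, with regression models only if needed. Under Sample size, 45 couples per group are raised to about 50 for attrition in each arm. Nothing says that excluded couples are followed up or analysed.

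**The concern.** The wording of the attendance criterion is awkward, but in a six-session programme the only sensible reading is that a couple is excluded once it has missed two or more sessions. A control couple has no sessions to miss. The rule therefore filters one randomised arm on behaviour after allocation and leaves the other unfiltered.

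That behaviour is plausibly related to the outcome. The questionnaires measure wives' sexual quality of life and marital satisfaction, and the sessions ask couples to attend sexual counselling together. Couples whose relationship is strained may be the ones who stop coming. If so, the remaining intervention couples would have scored better than the remaining controls even without counselling. A larger sample would not cure this, because it is selection and not chance.

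The rule also shifts the question. The stated hypothesis concerns couple counselling for wives of men with myocardial infarction, whereas the filtered comparison describes counselling among couples who attend at least five of six sessions.

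**Working it through.** **Inputs from the article (Sample size).** Means 81.30 and 82.70, difference 1.40; SDs 2.47 and 2.28; alpha 0.05 two-sided; power 80%; 45 couples per group, raised to about 50.

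**Reproducing the plan's figure.** n per group = (1.96 + 0.84)² × (2.28² + 2.47²) / 1.40² = 7.84 × 11.30 / 1.96 = 45.2, which agrees with the stated 45. (The printed formula shows 0.58 and lacks brackets round the variances; 0.84 with brackets is what yields 45. That is a separate matter.) Going from 45 to 50 implies a loss of 1 − 45/50 = 10%.

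**Planned effect in SD units.** Pooled SD = √((2.28² + 2.47²)/2) = 2.377, so 1.40/2.377 = 0.589 SD.

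**Bias from the rule.** Let f be the share of the intervention arm excluded for poor attendance, and g the amount in SD by which those women would have scored below the attenders with no counselling effect. The whole-arm mean is the attenders' mean minus f × g. Comparing attenders with an unfiltered control arm therefore adds f × g SD to the difference. Neither f nor g is in the article, so both are assumptions.

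**Type I error.** With 50(1 − f) against 50 couples, a common SD and no true effect, the standard error in SD units is √(1/(50(1 − f)) + 1/50). The noncentrality is f × g divided by it. For f = 20%, g = 1.0: √(1/40 + 1/50) = 0.212, and 0.20/0.212 = 0.943. The two-sided rejection rate is Φ(0.943 − 1.96) + Φ(−0.943 − 1.96) = 15.6%, or 15.4% from the noncentral t.

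| f | g | bias (SD) | share of 0.589 | type I, normal | type I, noncentral t |
|---|---|---|---|---|---|
| 10% | 0.25 | 0.025 | 4% | 5.2% | 5.2% |
| 10% | 0.5 | 0.05 | 8% | 5.7% | 5.7% |
| 10% | 1.0 | 0.10 | 17% | 7.8% | 7.7% |
| 20% | 0.5 | 0.10 | 17% | 7.6% | 7.5% |
| 20% | 1.0 | 0.20 | 34% | 15.6% | 15.4% |
| 30% | 1.0 | 0.30 | 51% | 27.5% | 27.0% |

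A negative g (couples who skip because they have few problems) gives the same magnitudes against counselling.

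**Power if everyone is kept.** Suppose a share q of the intervention arm attends poorly and gains nothing. The difference becomes 1.40 × (1 − q). With 50 analysed per arm, power = Φ(1.40(1 − q) / (2.377 × √(2/50)) − 1.96).

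| q | difference | power, 50 per arm | n per arm for 80% |
|---|---|---|---|
| 0 | 1.40 | 83.8% | 46 |
| 10% | 1.26 | 75.5% | 56 |
| 20% | 1.12 | 65.4% | 71 |
| 30% | 0.98 | 54.0% | 93 |

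**The case against.** The strongest reply is that the article is condensed and names no analysis population. Exclusion might mean only that a couple stops taking part, and an analysis plan not shown might analyse all couples as allocated. The silence on intention-to-treat is indeed no defect here. But the point rests on a rule the article states, not on something it leaves out. A later as-allocated definition would also conflict with that rule, and could not recover post-tests never collected from excluded women.

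Four stronger readings are tempting, and the document does not support them:

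- A reader might infer that attenders are compared with everyone. Controls can also leave, through withdrawal or moving city, and the attrition allowance covers both arms. Only the attendance rule is one-sided.
- A reader might take upward bias as established. The article gives no figure or sign for the prognostic gap, and couples with few problems may also skip sessions. Favouring counselling is plausible, not shown.
- A reader might count "living with the spouse during the study period" as another removal after allocation. It is listed as an inclusion criterion and can be read as a condition checked at entry; nothing says that couples who later separate are removed.
- A reader might take the larger scenarios as expected. The plan's own allowance implies about 10% loss, where the table's type I error is 5.2% to 7.8%.

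**Conclusion.** The concern holds for the attendance rule. It excludes couples on behaviour after allocation, in one arm only, and nothing stated in the article offsets it. The loss of randomised comparability follows from the design and does not depend on the direction of bias.

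The size is unknown. Under the assumed values, with no true effect, it runs from slight (0.025 SD, type I error about 5.2%) to about half the planned effect (0.30 SD, about 27%). These figures assume a common SD, 50 couples allocated per arm as in the abstract (the Sampling and data collection section says 45), and no selective loss among controls. Relocation and withdrawal are a lesser matter: they open both arms to loss after allocation, but neither is tied to one arm by its wording.

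This should be settled before follow-up, since a post-test that was not sought at the planned time cannot be replaced by analysis.

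**What to change.** 1. Delete missed sessions and relocation as grounds for exclusion from follow-up and analysis.
2. Seek the post-test from every allocated woman who has not withdrawn consent to data collection, whatever her attendance. The couples' telephone numbers are to be collected already.
3. Make the main analysis a comparison of women in their allocated arms, and treat those who withdraw as missing data.
4. Report attenders only as a secondary per-protocol analysis, with attendance counts.
5. Optionally, reword co-residence as a condition at enrolment.

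The direct cost is protocol wording and contacting non-attenders for one questionnaire round. The cost to disclose is statistical: the estimate may be smaller and power lower. If non-attenders gain nothing, power with 50 per arm falls from about 84% to about 76% at 10% non-attendance and about 65% at 20%. If non-attendance of that order is expected, the sample size should be revisited; 80% power would then need 56 or 71 analysed per arm.

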### Sample size

According to the study by Baqeri et al. [11], the average sexual satisfaction of spouses in the intervention group before intervention was 2.47 ± 81.30 and after intervention was 2.28 ± 82.70. Considering an alpha of 0.05 and 80% power, the sample size was estimated to be 45 couples in each of the two intervention and control groups. Taking into account potential sample attrition in each study arm (intervention and control), approximately 50 couples will be selected and included in the study.$$=\frac{{\left({z}_{1-\frac{\propto }{2}}+{z}_{1-\beta }\right)}^{2}\times {{\sigma }_{1}}^{2}+{{\sigma }_{2}}^{2}}{{\left({\mu }_{1}-{\mu }_{2}\right)}^{2}}=\frac{{\left(1.96+0.58\right)}^{2}\times {2.28}^{2}+{2.47}^{2}}{{(82.70-81.30)}^{2}}=\frac{7.89\times 5.19+6.10}{1.96}=45$$

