After preparing the counseling content for each session, we validated the developed content using the Delphi method based on feedback from reproductive health and cardiology experts at Urmia University of Medical Sciences. These experts possessed the necessary knowledge and skills in sexual counseling and essential care for heart patients. We conducted three rounds of questionnaires with a panel consisting of three cardiology specialists and three reproductive health specialists.

Interventions at the Cardiac Rehabilitation Center of Seyed Al-Shohada Hospital will be conducted with the presence of patients suffering from heart attacks and their spouses. The intervention will be in the form of discussions, group consultations, and individual consultations if needed, which will be presented at the end of the session.

The sessions will be managed by researchers who have the necessary skills and knowledge regarding sexual counseling. The topics of each session will be presented to the participants by the researchers. In this regard, the researcher will facilitate and guide the sessions. During the intervention, tools such as pamphlets, PowerPoint presentations, speeches, and couples counseling will be used to enhance the effectiveness of the intervention program.

First, the demographic information form is completed by the control and intervention groups, and then other questionnaires are completed by the women of both groups (pre-test). One month after the end of the intervention, the questionnaires will be completed again by women in the control and intervention groups (post-test).

**Table 1 Tab1:** Contents of counseling sessions based on the CHARMS method

No	The content of the session	Type of consultation
First	With a focus on establishing communication and building trust and collaboration between couples, evaluating the mental, emotional, and physical health of individuals, identifying their sexual problems, informing couples about the session structure and setting goals, educating on the sexual cycle, and familiarizing them with sexual performance and the internal and external organs of men and women. Defining sexual desire, arousal, lubrication, and orgasm, as well as familiarizing them with the sexual response pattern and explaining the physiological changes in men and women during sexual activity, including sexual positions.	Group

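### Couples can be excluded after allocation for missing counselling sessions; this rule can act only on the intervention arm and probably, though not certainly, favours counselling

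*Protocol article*

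**What the plan says.** Inclusion and exclusion criteria: "The exclusion criteria include not attending counseling sessions more than once and withdrawing from continued cooperation and changing the city of residence". The relocation item is tied to conduct in the trial: "changing the city of residence during the study period". I read the attendance item as missing more than one session.

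Abstract, Method: "Participants will be randomly allocated into two groups: control (50 couples) and intervention (50 couples"). The same paragraph gives the delivery format: "Couples in 6 groups of 8 members each will attend counseling sessions".

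Sampling and data collection: allocation is by a sealed envelope that the participants choose. The programme has six sessions: "it was arranged for them to be prepared for 6 sessions of sexual counseling based on the CHARMS method". Contact details are taken from the couples: "phone numbers will be collected for scheduling counseling sessions". The outcome visit is set for both arms: "One month after the end of the intervention, the questionnaires will be completed again by women in the control and intervention groups".

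Sample size: 45 couples per arm, raised for loss: "Taking into account potential sample attrition in each study arm (intervention and control), approximately 50 couples will be selected".

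Data analysis: the two groups are compared by independent t or Mann-Whitney tests. Nothing there says that couples meeting an exclusion criterion stay in the comparison.

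**The concern.** An exclusion criterion normally screens couples before allocation. These three cannot, because none of them can be known when the envelope is opened.

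The attendance item is the serious one. Only the intervention arm has sessions to miss, so the rule filters one arm on adherence and leaves the other untouched. Randomisation makes all allocated couples comparable. It does not make the compliant part of one arm comparable with the whole of the other.

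Sessions are attended jointly, and the outcomes are sexual quality of life and marital satisfaction. A link between missing sessions and a poor outcome is therefore plausible. If it exists, removing those couples lifts the intervention mean, which is the direction of the research hypothesis. A larger sample would not remove this bias, and post-tests that were never sought cannot be recovered at the analysis stage.

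The relocation item can act on either arm, but it discards women whose post-test could still be sought. Withdrawal can also occur in either arm and may mean refusing the questionnaires, in which case the loss is unavoidable.

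**Working it through.** **1. Timing and arm.** Allocation comes first; attendance, withdrawal and relocation come later. The described sessions serve 6 × 8 = 48 members. If members means couples, that is about one arm of 45–50. No sessions are described for controls, so it is an inference from the design that controls have none to miss.

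**2. The plan's own figure.** Inputs from Sample size: SDs 2.28 and 2.47, difference 82.70 − 81.30 = 1.40, two-sided alpha 0.05, power 80%.
- n per arm = (1.960 + 0.842)² × (2.28² + 2.47²) / 1.40² = 7.85 × 11.30 / 1.96 = 45.25, which agrees with the stated 45.
- Implied allowance: 1 − 45/50 = 10%, or 5 couples per arm. It protects power against loss and does nothing about bias.

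**3. How many couples the rule might remove.** The article gives no attendance rate. Assume each couple attends each of the 6 sessions independently with probability p. Then P(miss two or more) = 1 − p⁶ − 6(1 − p)p⁵.

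| p | share removed | of 50 couples |
|---|---|---|
| 0.95 | 3.3% | 1.6 |
| 0.90 | 11.4% | 5.7 |
| 0.85 | 22.4% | 11.2 |
| 0.80 | 34.5% | 17.2 |

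This model serves only to suggest plausible fractions. If attendance really were independent and identical across couples, missing sessions would be unrelated to outcome and the bias would be zero.

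**4. Bias if attendance is related to outcome.** A separate assumption is needed: a normal attendance propensity correlated ρ with the outcome, and the lowest fraction q removed from the intervention arm only. Bias = ρ·φ(z_q)/(1 − q) in SD units.
- q = 0.114: φ/(1 − q) = 0.193/0.886 = 0.218. For ρ = 0.2, 0.3, 0.5 the bias is 0.04, 0.07, 0.11 SD.
- q = 0.224: 0.299/0.776 = 0.385. The bias is 0.08, 0.12, 0.19 SD.
- q = 0.033: 0.073/0.967 = 0.076. With ρ = 0.2 the bias is 0.015 SD.

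Simulation of 40,000 trials, 50 per arm, no true effect; rate of significant results favouring counselling (nominal 2.5%):

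| q | ρ = 0.2 | ρ = 0.3 | ρ = 0.5 |
|---|---|---|---|
| 0.114 | 3.8% | 4.9% | 7.6% |
| 0.224 | 5.4% | 7.5% | 14.2% |

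At q = 0.033 and ρ = 0.2 the rate is about 3%.

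**5. Cross-check by a second route.** Let a fraction f of the 50 intervention couples be removed, with a mean g SD below attenders. Bias = f·g, and the standard error is √[1/(50(1 − f)) + (1 + f(1 − f)g²)/50].
- f = 10%, g = 0.5: bias 0.05 SD, SE 0.207, favourable false positives 4.3%.
- f = 20%, g = 0.5: bias 0.10 SD, 6.8%.
- f = 20%, g = 1.0: bias 0.20 SD, SE 0.220, 14.7%.
- g = 0: no bias, 2.5%.
- f = 20%, g = −0.5: bias −0.10 SD, 0.8%; counselling is now disadvantaged.

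Results are left in SD units. The 1.40-point difference and its SDs come from an earlier study's sexual satisfaction score, whereas the objectives name sexual quality of life (18–108) and marital satisfaction (47–235).

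**The case against.** **Direction.** A reader might infer that the comparison is certainly tilted towards counselling. The article does not support that. Nothing in it says that non-attenders would score worse. Couples who feel little need for help, or who miss sessions because of work or health, could score the same or better. This stands, so the direction is likely and not established.

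**Size.** No attendance rate or correlation is given, and the removal fractions come from a model under which the bias would be nil. The upper figure of 14% needs both 22% removed and a correlation of 0.5. Near the implied 10% loss, with correlation 0.2–0.3, the rate is about 4–5%. This stands, so the figures are illustrative.

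**One-sidedness.** A reader might infer that all three rules strip the intervention arm. Only the attendance rule does. Nor can withdrawers simply be telephoned: the numbers were taken for scheduling, and withdrawing from cooperation may include refusing the questionnaires.

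**Left to the analysis plan.** The analysis population and the missing-data method commonly belong in a plan not shown here, and the article gives the post-test for both arms without an attendance condition. It is fair that the lack of an intention-to-treat statement is no finding. The attendance rule is different, because it is stated. The article does not say outright that excluded couples leave the analysis, but exclusion criteria set beside an attrition allowance read that way. If they lead to no follow-up, no later plan can restore the data.

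**Conclusion.** The concern holds for the rule as written. The protocol fixes post-allocation exclusions, and one of them depends on adherence to a treatment that only one arm receives. Following it breaks the randomised comparison, and nothing elsewhere in the article offsets this.

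That conclusion rests on two readings: that controls have no sessions, and that excluded couples are neither followed up nor analysed. Both are the natural reading; neither is spelled out.

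The effect probably favours counselling. Over the assumed range it is 0.04–0.19 SD, with favourable false positives of about 4–14% against 2.5%. It is smaller at low loss and weak correlation, and nil or reversed if non-attenders would do as well or better. Confidence is high that the rule exists and is unsound, and much lower on the sign and size of its effect. It should be corrected before follow-up, because outcomes not collected cannot be recovered.

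**What to change.** - Remove non-attendance and change of residence as grounds for exclusion after allocation.
- Treat withdrawal as missing data only where the woman withdraws consent to data collection. Stopping the sessions is not by itself a reason to stop follow-up.
- Seek the one-month post-test from every allocated woman, whatever her attendance or address. Remote completion needs her agreement and care for privacy, given the subject matter.
- Analyse every couple in its allocated arm.
- Keep missing no more than one session solely as the definition of a per-protocol sensitivity analysis, labelled as such because it carries the selection described here.

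No new sample size follows. On the plan's own inputs, power is 79.8% with 45 per arm and 83.8% with 50.

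The cost is a short amendment, some extra follow-up effort, and possibly a smaller estimated effect, since couples who received little counselling stay in the intervention arm.
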